
### Intervention design: overview

#### The People’s War Against Pandemic intervention group 1

Participants are asked to use The People’s War Against Pandemic for a two-week intervention. Participants need to complete the storyline task at least once a day, watch at least one article and one video in the knowledge corner, and complete a retest of wrong choices in the intelligent evaluation module. Researchers check the completion of participants through the user management module, and those who fail to complete will be reminded by sending text messages or phone. The effect of the intervention will be evaluated by using the same questionnaire as applied in the baseline survey at week one and two of intervention. Before the training, participants will be informed that they will be rewarded with 50 RMB after completing daily tasks and questionnaire.

#### The People’s War Against Pandemic intervention group 2

Participants are asked to use The People’s War Against Pandemic for a four-week intervention. Other requirements are the same as those of intervention group 1. The effect of the intervention will be evaluated at week 1, 2, 3, 4 of intervention. The purpose of setting this group is to explore the optimal duration of the training, so that the participants will neither fail to achieve the training effect due to too short time nor get bored due to too long time.

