#### Control group

We established a QQ chat group and invited participants into this group. The same training resources as emergency preparedness training content index system and the knowledge corner are pushed to participants, and participants are required to study independently and complete online check-in for 2 weeks. Participants will be rewarded with 50 RMB after completing daily tasks and questionnaire, just like the intervention group. But this group does not have elements of storylines, virtual scenes, interactions and scoring.

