### Recruitment, randomization, and allocation concealment

#### Recruitment

Participants will be recruited through both online and on-site recruitment. The sample size calculation is based on the primary outcome: emergency preparedness of public for MEIDs. The sample size was performed using the formula developed by Chow [18], and the formula is as follows:$$\begin{array}{c}\mathrm{n}=2{\left(\sigma \frac{{z}_{1-\alpha /\left(2T\right)}+{z}_{1-\beta }}{{\mu }_{A}-{\mu }_{B}}\right)}^{2}\\ 1-\beta =\varphi \left(z-{z}_{1-\alpha /\left(2T\right)}\right)+{\varphi }\left(-z-{z}_{1-\alpha /\left(2T\right)}\right), z=\frac{{\mu }_{A}-{\mu }_{B}}{\sigma \sqrt{\frac{2}{n}} }\end{array}$$

The significance level of the test is α = 0.05, the test power is 1-β = 0.8, standard deviation is = 26.31, the number of comparisons to be made is T = 3, is the standard Normal distribution function. Calculator software (Power and Sample Size) was used to calculate the initial sample size N1 = 171. Considering the attrition rate of 20%, the sample size of each group was increased to 206, and the total sample size of the three groups was 618.

The study will be conducted in Luzhou City, Sichuan Province, China. Participants were recruited from the community and signed informed consent forms if they agreed to participate in the study and complete follow-up measurements. After completing the study, each participant will receive a reward of 50 RMB in cash.

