### Outcomes and data collection

The primary outcome is emergency preparedness of public for MEIDs. The secondary outcome is prevention and control knowledge of MEIDs. The assessment of intervention group 1 will be conducted at baseline, week one and two of the intervention, and 1, 3, 6 months after the intervention. Assessment of the intervention group 2 will be conducted at baseline, week 1, 2, 3, 4 of intervention, and 1, 3, 6 months after the intervention. Assessment of the control group will be conducted at baseline, week one and two of the intervention, and 1, 3, 6 months after the intervention. In addition, participants' evaluation of the virtual interactive training system will be assessed at the completion of the intervention. Study schedule of enrolment, interventions, and assessments is shown in the Fig. 3.

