### Limitations

As with any research design, the trial also has potential limitations. In the follow-up observation, the time may be too long, to loss of participants. We can reduce the dropout rate by strengthening the connection with participants or giving appropriate rewards. In addition, The People’s War Against Pandemic has a scoring element, and participants may be addicted to pursuing high scores. To address this problem, we can limit the time of training every day.

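### Staff reminders are described for the two platform groups only, and the 50 RMB reward is given two different conditions, so adherence, and possibly questionnaire return, may differ between arms

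*Protocol article*

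**What the plan says.** **Reminders.** Under Intervention design: overview, researchers follow group 1's task completion through the platform's user management module, and "those who fail to complete will be reminded by sending text messages or phone". For the four-week group the article adds "Other requirements are the same as those of intervention group 1", so the checks and reminders carry over. Under Control group, "participants are required to study independently and complete online check-in for 2 weeks". These participants are in a QQ chat group where learning material is pushed to them; no reminder is described.

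**Reward.** Before training, group 1 "participants will be informed that they will be rewarded with 50 RMB after completing daily tasks and questionnaire". For control: "Participants will be rewarded with 50 RMB after completing daily tasks and questionnaire, just like the intervention group". The Recruitment section states it differently: "After completing the study, each participant will receive a reward of 50 RMB in cash".

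**Assessments.** "Assessment of the control group will be conducted at baseline, week one and two of the intervention, and 1, 3, 6 months after the intervention". Group 1 has the same schedule. Group 2 is also assessed at weeks 3 and 4.

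**Attrition.** The sample size allows 20% loss with no distinction by arm, and the statistical section relies on intention-to-treat to deal with attrition. Under Limitations: "We can reduce the dropout rate by strengthening the connection with participants or giving appropriate rewards".

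**The concern.** The Discussion takes the comparison with control as a test of the platform against self-directed study. If staff chase non-completers in the platform groups only, part of any difference may come from being chased. The Control group section says what control lacks (the narrative, virtual environment, interactivity and scoring features), and staff contact is not in that list. A reader would therefore assume that contact is balanced.

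The reward raises a different issue. Intention-to-treat needs outcome data from people who stopped doing the tasks. A payment that depends on daily tasks gives exactly those people less reason to answer the later questionnaires. A payment for completing the study, which runs to six months after the intervention, works differently. The article states both conditions and does not say which one triggers payment, or whether there is one payment or two. Group 2's heavier load for apparently the same sum bears on the two-week versus four-week comparison, which is the trial's first hypothesis and its basis for choosing a duration.

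**Working it through.** The plan gives no figure for reminders, payment or arm-specific loss, so most of the check sets the sections side by side.

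**1. Terms by arm, as described**

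| | Group 1 | Group 2 | Control |
|---|---|---|---|
| Required days | 14 | 28 | 14 |
| Completion checked by researchers | yes | yes (inherited) | online check-in |
| Text or phone reminder | yes | yes (inherited) | none described |
| Reward, arm section | 50 RMB, tasks and questionnaire | apparently the same (inherited) | 50 RMB, tasks and questionnaire |
| Reward, Recruitment section | 50 RMB, study completed | same | same |
| Assessments including baseline | 6 | 8 | 6 |

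Assessments are baseline + weeks 1 and 2 + months 1, 3 and 6 = 6 for group 1 and control. Weeks 3 and 4 bring group 2 to 8.

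Group 1 and control differ in reminders and not in reward. Groups 1 and 2 differ in load and not, as far as stated, in reward.

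**2. Reward per required day.** 50/14 = 3.57 RMB in group 1 and control; 50/28 = 1.79 RMB in group 2, which is half.

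**3. Would unequal loss mainly cost power?** The mean difference behind N1 = 171 is not given, so 171 cannot be reproduced forwards. Solving the article's formula backwards, with SD 26.31, T = 3, α = 0.05 and power 0.80:

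difference = 26.31 × √(2/171) × (z at 1 − 0.05/6 + z at 0.80) = 26.31 × 0.1081 × (2.394 + 0.842) ≈ 9.21 points (0.35 SD).

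Starting from 206 per arm, power at that difference under assumed losses is:

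| Loss, control / intervention | Remaining | Power |
|---|---|---|
| 20% / 20% | 164.8 / 164.8 | 0.78 |
| 25% / 15% | 154.5 / 175.1 | 0.78 |
| 30% / 10% | 144.2 / 185.4 | 0.78 |
| 30% / 20% | 144.2 / 164.8 | 0.75 |
| 40% / 10% | 123.6 / 185.4 | 0.73 |

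With average loss held at 20%, imbalance barely changes power. The issue is bias.

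**4. Illustration of bias (assumed inputs throughout).** A completers-only mean differs from the full-arm mean by loss × (completers' mean − lost participants' mean). Suppose loss is 15% in one arm and 30% in group 2, and lost participants score 0.25 to 0.75 SD lower. The spurious difference between arms is then

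(0.30 − 0.15) × (0.25 to 0.75) × 26.31 = 0.99 to 2.96 points,

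or 11% to 32% of the back-solved 9.21. With equal loss and the same gap in both arms it is zero. This describes an analysis of completers and only the extra loss in group 2. It says nothing about the effect of reminders.

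**The case against.** A reader might infer that adherence and missing data will differ by arm. The document does not show that. Control is paid on the same terms as group 1 over the same two weeks, so the reward alone cannot separate them. The reminders concern daily tasks done on the platform, whereas outcome questionnaires are collected on a separate survey service, and no questionnaire reminder is described for any arm. A link from task reminders to missing outcomes is possible but indirect. The retention measures under Limitations are not tied to any arm.

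A reader might also infer that control is never chased. The article condenses a fuller protocol, and the QQ group with its check-in is a working contact channel, so silence is not proof. What stands is that the article takes care to state equal reward and to list what control lacks, and mentions reminders in neither place. One could regard reminders as part of the training package. In that case the comparison is of platform plus prompting with self-study, and the conclusion should say so.

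On payment, the two statements can be read as one rule: what must be done, and when the cash is handed over. No forfeiture or threshold is stated, so the claim that anyone who misses a task loses the money goes beyond the text. Even so, completing tasks and completing the study are different conditions. Someone who skips tasks but returns every questionnaire is paid under one reading and not under the other.

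**Conclusion.** The point holds in a limited form. As described, staff reminders go to the two platform groups and not to control, so the platform contrast includes prompting and adherence may differ by arm. The reward condition is stated in two ways that need reconciling. If it depends on daily tasks, participants who fall behind may have less reason to return outcome data, and group 2 does twice the required days and two more assessments for apparently the same 50 RMB.

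The direction and size of any bias cannot be computed from the document. The 1.0 to 3.0 points above rest on assumed loss rates, an assumed score gap and a completers-only analysis, and the 9.21-point yardstick is back-solved from N1 = 171 and stated nowhere. These figures show what unequal loss could do and are not an estimate for this trial. The finding is a cheap improvement and not a flaw that invalidates the design.

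**What to change.** 1. Send control participants who miss a check-in the same text or phone reminders as the platform groups, on the same trigger. If this is already done, say so under Control group.
2. Reconcile the arm descriptions and the Recruitment section to one reward rule: the 50 RMB is paid for returning the scheduled outcome questionnaires in every arm, regardless of daily-task completion. State whether there is one payment or two, and whether group 2 receives the same sum.

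The cost is a few more messages and possibly slightly lower daily-task adherence, since payment would no longer depend on the tasks. Recruitment began in July 2022 and participants are told the terms before training, so those already enrolled keep the terms they were given, and the date of the change should be recorded. A flat payment does not remove group 2's heavier load for the same money, so that caveat remains for the duration comparison.

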## Methods

### Study design

The design type of this study is a randomized controlled trial. Study participants will be recruited from public volunteers and allocated to one of the three randomized groups after completing a baseline survey (Fig. 1) (The People’s War Against Pandemic intervention group 1, The People’s War Against Pandemic intervention group 2, Control group). Three follow-up visit assessments are required to complete for participants at four weeks later, three months and six months after the intervention. Our hypotheses are:There is no statistical difference between The People’s War Against Pandemic intervention group 1 and The People’s War Against Pandemic intervention group 2 in prevention and control knowledge of MEIDs and emergency preparedness of MEIDs.Comparing The People’s War Against Pandemic intervention group 1 and Control group, the former group will have better effect on improve prevention and control knowledge of MEIDs and emergency preparedness of MEIDs.Comparing The People’s War Against Pandemic intervention group 2 and Control group, the former group will have better effect on improve prevention and control knowledge of MEIDs and emergency preparedness of MEIDs.

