### Data management and statistical analysis

Data will be collected, recorded and managed by the Survey Star, an online questionnaire platform (www.wjx.cn, Changsha Ranxing Information Technology Co., Ltd in China) to ensures the safety, integrity and consistency of the data. Researchers will download the data from Survey Star and save it in text format to a password-protected server. SPSS 21.0 analysis software was used for data analysis by the third party who did not participate in the intervention.

Data will be collected at baseline and descriptive statistics will be used to show the characteristics of each arm at baseline. The outcome indicator prevention and control knowledge of MEIDs is a binary variable, so the chi-square test will be used to compare among the three arms at the intervention completion, 1, 3, and 6 months after the intervention. Analysis of Variance (ANOVA) will be used to find out whether there are differences among the three arms in the outcome indicator-emergency preparedness of public for MEIDs. Repeated Measures ANOVA will be used to measure weather there are differences in emergency preparedness of public for MEIDs score at 1, 3, and 6 months after intervention. A Bonferroni correction will be used for multiple testing. Intention-to-treat analysis will be used to account for the influence of attrition. The difference was statistically significant when *P* ≤ 0. 05.

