Three arms were designed in this research, including two intervention arms and one control arms. Participants in the two intervention groups will receive The People’s War Against Pandemic to complete the storyline task at least once a day, read at least one article and watch one video in the knowledge corner, and complete a retest of wrong choices in the intelligent evaluation module. The difference between the two groups is the intervention time. Due to the interactivity of virtual interactive training system, participants may have different outcomes in different training. To explore the optimal duration to finish all the outcomes, we designed two-week and four-week groups, so that the participants will neither fail to achieve the training effect due to too short time nor get bored due to too long time. By comparing the intervention groups with the control group, it can be found whether The People’s War Against Pandemic is better than autonomous learning in improving emergency preparedness of MEIDs for public. By comparing the two intervention groups, we can find out the optimal duration to improve emergency preparedness of MEIDs for public.

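### Two randomised durations can show whether four weeks differs from two but cannot find the optimal duration, and the interim weekly scores that bear on it appear in no named analysis

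*Protocol article*

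**What the plan says.** Under Intervention design: overview, group 1 trains for two weeks and group 2 for four, with otherwise identical requirements. On group 2 the article says "The purpose of setting this group is to explore the optimal duration of the training". The Discussion repeats the aim of exploring duration and then claims more: "By comparing the two intervention groups, we can find out the optimal duration to improve emergency preparedness of MEIDs for public".

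Hypothesis 1 (Study design) expects the arms not to differ: "There is no statistical difference between The People’s War Against Pandemic intervention group 1 and The People’s War Against Pandemic intervention group 2", for both knowledge and preparedness. It gives no margin.

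For group 2, "The effect of the intervention will be evaluated at week 1, 2, 3, 4 of intervention". According to Outcomes and data collection, group 1 and control are assessed during training at weeks 1 and 2 only. All arms are then followed up at 1, 3 and 6 months after their intervention ends.

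Data management and statistical analysis compares knowledge at completion and at the three follow-up times. The repeated measures ANOVA of preparedness takes the "score at 1, 3, and 6 months after intervention". A further ANOVA compares preparedness among the three arms without naming a time.

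**The concern.** The Discussion presents finding the optimum as something the two-arm comparison can deliver. An optimum is a feature of the curve of score against duration, and two randomised points do not determine that curve. The article predicts no difference between the points, which is the result least able to place an optimum.

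The data closest to the question are the scores taken during training, because they show whether gains are still growing. The named analyses do not mention the interim ones.

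At stake is the conclusion about the third arm, 206 people. Followed as written, the report could name an optimal duration that the design cannot identify, or read a non-significant difference as proof that two weeks is enough. A group 2 advantage could also be credited to longer training when part of it comes from meeting the same questions more often.

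**Working it through.** **Inputs** (Recruitment section): SD 26.31, alpha 0.05, power 0.80, T = 3 comparisons, 171 per group before attrition, 206 after, 618 in total. These concern the preparedness score.

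**The plan's own figures.** The mean difference appears only as a symbol in the text at hand, so 171 cannot be reproduced forwards. Solved backwards:
- standard error of a two-arm difference = 26.31 x sqrt(2/171) = 2.845
- difference = (2.394 + 0.842) x 2.845 = 9.2 points, where 2.394 is the normal quantile for 0.05/(2 x 3)
- attrition step: 171 x 1.2 = 205.2, rounded up to 206; 3 x 206 = 618

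**Precision of four versus two weeks, 171 per arm.**
- 95%: 1.96 x 2.845 = 5.6 points
- Bonferroni: 2.394 x 2.845 = 6.8 points
- Range: 5.7 and 7.0 with 164 per arm; 5.1 and 6.2 with 206
- Power at the Bonferroni level: 80% for a true difference of 9.2 points, 51% for 6.9, 22% for 4.6, 6% for 2.3

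A non-significant result is therefore likely even when the durations differ by several points.

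**What the two points can say.** Suppose the score rises to a single peak or plateau.
- Equal means at 2 and 4 weeks fit a plateau reached before week 2, a plateau from week 2, or a peak at week 3.
- A higher mean at 4 weeks fits a peak at 3 weeks, at 4 weeks, or later.
- A higher mean at 2 weeks fits a peak before 2 weeks, at 2 weeks, or between 2 and 4.

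No result singles out one duration.

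**Assessments against named analyses.**

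| Score | Group 1 | Group 2 | Control | Named in the analysis section |
|---|---|---|---|---|
| Week 1 | yes | yes | yes | no |
| Week 2 | completion | interim | completion | presumably, as completion, in group 1 and control only |
| Week 3 | none | interim | none | no |
| Week 4 | none | completion | none | presumably, as completion |
| 1, 3, 6 months | yes | yes | yes | yes |

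Group 2's week 2 score, the one that matches group 1's completion score in time and training received, is among those not named.

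**Number of tests.** Group 2 answers 1 + 4 + 3 = 8 times; the other arms answer 1 + 2 + 3 = 6 times. The intervention section says the baseline questionnaire is reused. At its completion score group 2 is on its fifth attempt and group 1 on its third.

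**What the weekly scores could give.**
- Pooling groups 1 and 2 against control at weeks 1 and 2: 26.31 x sqrt(1/342 + 1/171) = 2.46, against 2.845 for one arm versus control. The ratio is sqrt(0.75) = 0.87, so the standard error is 13% smaller.
- Change between two weekly scores within group 2, 95% half-width 1.96 x 26.31 x sqrt(2(1 - rho)/171): 3.9, 3.1 and 2.5 points for rho = 0.5, 0.7 and 0.8. The correlation is my assumption; the article gives none. This is a within-arm quantity and does not replace the randomised contrast.

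**The case against.** The intervention section says only that duration will be explored. The Discussion says "we designed two-week and four-week groups" and can be read as choosing between the two durations tested. The article has about one paragraph of statistics, and the modelling of interim scores is commonly left to a fuller plan. Group 2's weekly course is not randomised, and adding questionnaires after recruitment began in July 2022 would change a running schedule.

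Much of this stands. It makes the interim-score part a matter of what the article names, not proof that those scores will go unused, and it makes the extra questionnaires optional. It does not rescue the Discussion sentence, which claims more than either reading of the design supports. A fuller analysis plan could not remove the difference in number of tests, because the assessment schedule fixes it.

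Three stronger readings are tempting and not supported:
- That the weekly scores enter no analysis. The last one in each arm is presumably the completion score used for knowledge, and the preparedness ANOVA names no time, so it excludes none of them.
- That the trial will say nothing about duration. Group 1 versus group 2 is hypothesis 1, presumably one of the three comparisons in the sample size, and falls under the ANOVA.
- That the weekly questionnaires are the only data on levelling off. The training system also records scores, time and choices in the intervention groups.

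**Conclusion.** The point holds in this form. The design can estimate the difference between four and two weeks of training to within about 5.6 points (6.8 at the Bonferroni level). It cannot find the optimal duration, and a non-significant difference would not establish equivalence. The interim scores (week 1 in all arms, weeks 2 and 3 in group 2) have no named analysis. Any group 2 advantage includes an unknown share of practice from two extra administrations; the documents give nothing from which to size that share.

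The figures assume the planning SD of 26.31 and 171 analysed per arm. Treating week 2 (group 1, control) and week 4 (group 2) as the completion scores is an inference from the schedule. The comparisons of each intervention arm with control, and the sample size, are not changed by this point.

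**What to change.** 1. **Restate the aim** in the group 2 paragraph and the Discussion: to estimate the difference in preparedness between four and two weeks of training, with a confidence interval. Reconcile this with hypothesis 1, and state that non-significance will not be read as equivalence or as an optimum. Cost: wording only.
2. **Analyse the weekly scores already scheduled** in one longitudinal model. Pool groups 1 and 2 against control at weeks 1 and 2, when their requirements are the same. Report group 2's changes from week 2 to 3 and from week 3 to 4 with confidence intervals, labelled as exploratory, within-arm and subject to practice effects. Cost: a little analysis work and no new data.
3. **Optional, if the stage of recruitment allows:** send the same online questionnaire to group 1 and control at weeks 3 and 4, so that groups 1 and 2 can be compared at equal time since the start and after equal numbers of tests. Cost: a schedule amendment and a small respondent burden, at most 2 x 2 x 206 = 824 further questionnaires. Participants already past week 4 could not be covered. Items 1 and 2 do not depend on it.
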